## Discussion

The W-shaped excitability framework—where both hyper- and hypo-excitability impair function—doesn't map neatly onto post-stroke spasticity (28). Stroke does not produce a uniform excitability shift; it may create a spatially dissociated pathology characterized by spinal hyperexcitability in spastic flexors and, as suggested by our pilot data and others, cortical hypo-excitability in their antagonists; accordingly, this “split-modulation” approach emerged from pilot data (*n* = 12) where cTBS alone reduced MAS scores without improving ARAT, and iTBS alone did the opposite—suggesting that resetting the network requires both levers (28).

Parameter selection bypassed convention in favor of peripheral nerve physiology. The 110%−120% PMT intensity—averaging 38.4% MSO in our pilot—produced a 15%−20% increase in M-wave amplitude, the narrow band where Ia fibers activate without recruiting nociceptive afferents (20). Below this threshold, spinal plasticity markers (H-reflex suppression) vanished on TMS-EEG (27); above it, tolerance dropped below 70% within 15 min. The 600-pulse dose was selected based on a balance between efficacy and safety. The IFCN guidelines recommend a maximum of 800 pulses per session for peripheral TBS protocols to ensure safety (17). Furthermore, doses of 400–800 pulses have been commonly employed in prior rPMS studies and are considered necessary to induce consistent neurophysiological changes at the spinal level, such as H-reflex suppression (11, 21). Thus, our 600-pulse protocol operates within established safety boundaries while aligning with doses used in effective rPMS studies.

The distinctive sounds and sensations produced by the active stimulation device posed a significant risk to blinding. To counter this, we implemented a comprehensive strategy. We engineered the sham coil to replicate the sensory profile of the active device and added random timing jitter to mask its rhythmic pattern. This technical approach cut the rate of correct group identification in our pilot study from 38 to 17%. Concurrently, we administered deceptive questionnaires about non-existent sensory details, a tactic that reduced participants' confidence in their guesses to chance levels. We will formally assess unblinding at the trial's conclusion and perform sensitivity analyses to gauge its influence on outcomes. For assessors, blinding was secured by physically separating them from the intervention suite, encrypting all group assignments, and employing multiple independent raters.

A single-center study with a modest sample size (*n* = 54) may limit the generalizability of our findings. Rather than dilute inclusion criteria, we embedded a mechanistic substudy in the first 30 participants: simultaneous TMS-EEG and spinal H-reflex recording to build a Bayesian hierarchical model linking individual excitability profiles to response (27). This won't boost statistical power but provides a prior for phase II trials, preventing wasted resources on suboptimal doses.

To further explore the long-term effects, a future 6-month substudy (*n* = 20) is planned. This substudy will not merely extend observation—it will use wearable EMG to continuously track the time constant of long-term trajectory of spasticity. This would reveal whether durability requires periodic booster sessions, directly informing translational decisions (home-based vs. clinic-based devices).

Based on our pilot study (unpublished), we identified a “high neural noise” phenotype, characterized by PMT variability (CV > 15%) in 23% of participants. Rather than treating this as statistical noise, we will use it as a predictive feature: poor responders with high CV will signal the need for EMG-closed-loop titration in future protocols. This is an adaptive design element nested within the trial logic, not a *post-hoc* fix.

Positive results remain contingent on three unresolved conditions: (1) Technical—can the dual-coil apparatus be miniaturized into a wearable? (2) Physiological—does efficacy depend on residual corticospinal integrity (do absent MEPs preclude benefit)? (3) Economic—does cost-effectiveness outperform botulinum toxin plus therapy in real-world settings (3, 29)? We are collaborating with a manufacturer on a dual-channel pTBS prototype, but the design metric isn't power output, but rather minimizing the “acoustic fingerprint” that undermines blinding. This engineering constraint may prove the study's most commercially relevant byproduct.

Ultimately, this RCT tests whether the W-shaped model's “optimal zone” exists at the individual level (28). Aggregated group means are secondary; single-subject excitability shifts determine the model's survival.

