**Methods:**

This single-center, three-arm, sham-controlled, single-blind randomized controlled trial enrolled 54 stroke survivors (aged 40–80, 3–12 months post-stroke, Modified Ashworth Scale score ≥1). Participants were randomized in a 1:1:1 ratio to receive a 10-session intervention over 2 weeks (5 days/week). Each session consisted of stimulation followed by 30 min of conventional physical therapy. The stimulation protocols were: Group 1: active iTBS over extensor carpi radialis longus + sham cTBS over flexor carpi radialis; Group 2: sham iTBS + active cTBS; Group 3: active iTBS + active cTBS. Stimulation was delivered using a MagTD stimulator at 110%−120% of the peripheral motor threshold (mean 38.4% maximum stimulator output), with 600 pulses per session (50 Hz burst frequency, 5 Hz theta rhythm).

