### Theta burst stimulation protocol targeting antagonist and spastic muscles

The flexor carpi radialis (FCR) and extensor carpi radialis longus (ECRL) were selected as stimulation targets based on their established role as a primary agonist-antagonist pair responsible for the wrist flexion-extension imbalance in post-stroke upper limb spasticity. The central mechanistic hypothesis is that the spatial proximity of their cortical representations within the primary motor cortex enables the simultaneous modulation of this pair to preferentially target a shared cortical microcircuit, thereby regulating its excitatory-inhibitory balance to reset abnormal motor output (16).

All enrolled participants will receive iTBS, cTBS or sham stimulation before CPT session each weekday, Group 1: active iTBS to the antagonist plus sham cTBS to the spastic muscle. Group 2: sham iTBS to the antagonist plus active cTBS to the spastic muscle. Group 3: active iTBS to the antagonist plus active cTBS to the spastic muscle (Figure 2). The intervention will last for two consecutive weeks, with all procedures strictly adhering to the 2021 safety guidelines issued by the International Federation of Clinical Neurophysiology (17). Stimulation will be delivered with a MagTD transcranial magnetic stimulator (MagTD; Wuhan Yiruide Medical Device Technology Co., Ltd., Wuhan, China) and a figure-of-eight double coil (maximum field strength = 2 T, diameter = 9 cm). The coil center will be placed tangentially over the target muscle group, with the induced current directed downward. For the sham stimulations, we choose the Magstim's70 mm figure-of-eight double rapid2 air cooled coil (P/N 3910-00 S/NO 728) (18). The coils were identical in external appearance which ensured that the patients remained blind to the intervention (Figure 3).

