The iTBS protocol was configured to deliver a total of 600 pulses, organized into 20 trains. Each train consisted of 10 bursts, with an 8-s inter-train interval. Within each burst, three pulses were administered at a frequency of 50 Hz, and the bursts themselves were repeated at a theta frequency of 5 Hz. The total stimulation duration for the iTBS protocol was 200 s (Table 3). During treatment, participants will lie supine. For iTBS: the figure-of-eight double coil will be centered over the antagonist muscle—specifically, the most prominent belly of the extensor carpi radialis longus (ECRL), located 4 cm distal to the lateral epicondyle of the humerus and 1 cm radially (Figure 2). This location was confirmed through anatomical palpation and is standardized to ensure consistent targeting of the ECRL muscle belly, a common motor point for effective stimulation (20, 21). The coil plane will be flush with the skin surface, the handle oriented proximally and angled aligned parallel to the long axis of the forearm. The cTBS protocol was configured to deliver a total of 600 pulses in a single, continuous train of 200 bursts without interruption. The total stimulation duration for cTBS was 40 s, during which bursts were delivered continuously at a theta frequency of 5 Hz. Each burst contained three pulses administered at a frequency of 50 Hz. For cTBS: the coil will be centered over the spastic muscle—the most prominent belly of the flexor carpi radialis (FCR), located 5 cm distal to the medial epicondyle of the humerus and 1 cm ulnarly. Similarly, this site was determined based on anatomical landmarks to reliably target the FCR belly, promoting reproducible stimulation across sessions (20, 21). The coil plane will again lie flat against the skin, with the handle oriented proximally and aligned parallel to the long axis of the forearm. The stimulation intensity for both iTBS and cTBS was set at 110%−120% of the individual's peripheral motor threshold (PMT).

**Table 3 T3:** Detailed parameters for the peripheral theta-burst stimulation protocols.

**Parameter**	**iTBS**	**cTBS**
Total stimulation duration	200 s	40 s
Total pulses	600	600
Pulse frequency (within burst)	50 Hz	50 Hz
Pulses per burst	3	3
Burst frequency	5 Hz	5 Hz
Bursts per train	10	200
Total trains	20	1
Inter-train interval	8 s	N/A
Stimulation intensity	110%−120% of PMT	110%−120% of PMT

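### The stated 600 pulses per session, and the claim of staying under the cited 800, do not cover Group 3, which receives 1,200 active pulses per session

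*Protocol article*

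**What the plan says.** The Methods paragraph of the abstract lists the three arms and then gives one dose for the stimulation, "with 600 pulses per session". It describes a session as the stimulation together with the 30 minutes of conventional physical therapy (CPT) that follow it.

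The section on the theta burst stimulation protocol sets the daily schedule: "All enrolled participants will receive iTBS, cTBS or sham stimulation before CPT session each weekday". It defines the combined arm as "Group 3: active iTBS to the antagonist plus active cTBS to the spastic muscle". It also commits the trial to the guideline, "with all procedures strictly adhering to the 2021 safety guidelines issued by the International Federation of Clinical Neurophysiology".

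The dose paragraph above Table 3 treats the two protocols separately. For one, "The iTBS protocol was configured to deliver a total of 600 pulses"; for the other, "The cTBS protocol was configured to deliver a total of 600 pulses". Table 3 repeats this with 600 in each column.

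The Discussion defends the dose on safety grounds. It states that "The IFCN guidelines recommend a maximum of 800 pulses per session for peripheral TBS protocols to ensure safety", adds that 400 to 800 pulses are common in earlier peripheral stimulation studies, and concludes that "our 600-pulse protocol operates within established safety boundaries". No arm is excepted.

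**The concern.** The abstract's figure and the Discussion's conclusion both treat 600 as the amount delivered in a session. That is true where one of the two protocols is sham. In Group 3 both are active, so the session total is the sum of two 600-pulse protocols.

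Two statements are affected. The first is a plain dose statement: the abstract gives a per-session figure that is wrong for one arm, whatever the guideline says. The second is a safety statement: a limit quoted per session is compared with a dose that is per session in only two of the three arms.

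Group 3 is the arm the trial expects to do best. A reader, an ethics reviewer or a team repeating the trial can work out its dose from the arm definitions and Table 3, but cannot tell from the article whether that dose is within the limit the article relies on. No endpoint, comparison or sample-size figure depends on this point.

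**Working it through.** **Inputs**

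- iTBS: 20 trains, 10 bursts per train, 3 pulses per burst (Table 3 and the paragraph above it).
- cTBS: 1 train, 200 bursts, 3 pulses per burst (same place).
- Arms: Group 1 active iTBS with sham cTBS; Group 2 sham iTBS with active cTBS; Group 3 both active (theta burst stimulation protocol section).
- Sessions: five a week, 10 in total (Study design).
- Limit as the article cites it: 800 pulses per session (Discussion).

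**Step 1: reproduce the stated 600.** Pulses = trains × bursts per train × pulses per burst.

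- iTBS: 20 × 10 × 3 = 600.
- cTBS: 1 × 200 × 3 = 600.

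The 600 is exact for each protocol taken alone.

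**Step 2: confirm that both protocols fall in one session.** Two weeks of five weekdays gives 2 × 5 = 10 stimulation days, which equals the stated 10 sessions. Stimulation precedes therapy on each of those days. Nothing says that the 600 is divided between the two muscles or that the protocols alternate by day.

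**Step 3: sum active pulses by arm**, counting sham as zero, and compare with 800.

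| Arm | Active pulses per session | Share of 800, per-session reading | Share of 800 at each actively stimulated site, per-site reading | Active pulses over 10 sessions |
|---|---|---|---|---|
| Group 1 | 600 + 0 = 600 | 600/800 = 75% | 75% | 6,000 |
| Group 2 | 0 + 600 = 600 | 600/800 = 75% | 75% | 6,000 |
| Group 3 | 600 + 600 = 1,200 | 1,200/800 = 150% | 75% | 12,000 |

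On the per-session reading Group 3 is 1,200 − 800 = 400 pulses above the cited limit. Its session total is also above the 400 to 800 range that the Discussion offers as usual practice.

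**The case against.** The strongest reply is that the dose is fully specified where it counts. The arm definitions and Table 3 leave a therapist in no doubt about what to deliver, and the abstract's figure is shorthand for a parameter that both protocols share. On the limit, the article uses the word protocol mostly for iTBS and cTBS separately, and the sentence that cites the 800 refers to peripheral TBS protocols. The 600-pulse protocol may therefore be compared, like for like, with a limit per protocol or per site. The Introduction supports this reading: it says earlier work mainly stimulated the spastic muscle alone, so the 400 to 800 range probably describes mainly single-site doses. The ethics committee approved the trial and may have seen the combined dose in a fuller document. Threshold titration and M-wave checks, together with the adverse-event recording and stopping rule under Safety measurements, limit any practical harm.

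Much of this stands. The delivered dose is not in doubt, the per-site reading is plausible, and no harm or breach has been shown. Three things remain. The per-site reading is stated nowhere: the limit is worded per session, and the abstract describes a session as the whole stimulation-plus-therapy visit. Even if the per-site reading is right, it rescues only the safety claim, because the abstract's per-session figure is still wrong for Group 3. And the monitoring measures reduce risk without correcting either statement. Nor can this be put down to an article condensing a longer protocol, since a dose and a compliance conclusion are stated and do not fit other stated text.

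**Conclusion.** The concern holds. That Group 3 receives 1,200 active pulses per session, twice the abstract's figure, follows from the article's own parameters and does not depend on the guideline. As worded, the conclusion that the dose is within the cited limit covers Groups 1 and 2 only. For Group 3, 18 of 54 planned participants, the dose is 150% of the limit if the limit is per session, or 75% at each site if it is per site.

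This rests on three assumptions: sham contributes no active pulses; the 600 is not split between sites and the protocols do not alternate by day, for which the text gives no sign; and the 800 is taken only as the article cites it. Which reading of the limit is correct cannot be settled without the guideline, so neither non-compliance nor an unsafe dose is established. The correction is worth making because it concerns a stated dose and a safety claim for the main experimental arm.

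**What to change.** 1. In the abstract and Table 3, state active pulses per session by arm: 600 for Group 1, 600 for Group 2 and 1,200 for Group 3 (600 at each of two sites).
2. Check the cited guideline (reference 17) and state in the Discussion whether the 800 applies per site or per session.
3. If it is per site, say so and give the dose as 600 at each site.
4. If it is per session, withdraw for Group 3 both the within-limit conclusion in the Discussion and the strict-adherence statement in the stimulation section. Give the ethics committee an explicit justification for 1,200 pulses, unless it has already reviewed the combined dose.

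The cost is small. On the per-site branch it is short text corrections and one look at the guideline. The per-session branch adds one further text correction and a written justification. The intervention, assessments and analysis stay as they are, and nothing in the article alone supports changing the dose.

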### Sample size estimation

As the differential effects of priming iTBS on hemiparetic upper-limb training have yet to be examined, we based our sample-size estimate on existing three-group trials. A recent meta-analysis reported a pooled Cohen's *d* = 0.60 favoring iTBS for upper-limb motor improvement. For a three-group design, this translates to an effect size *f* of ~0.30 (15). *A priori* power analysis (power = 0.80, two-tailed α = 0.05) indicated that 45 participants would be required. Accounting for an anticipated 15% dropout rate, we will recruit 18 participants per group, for a total sample size of 54. This recruitment target is expected to yield at least 45 participants completing the trial.

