**Figure 3 F3:**
[figure not shown]
Schematic of peripheral coil placement for the three trial arms. Group 1 **(top)**: Active iTBS over ECRL (antagonist) + sham cTBS over FCR (spastic muscle). Group 2 **(middle)**: Sham iTBS over ECRL + active cTBS over FCR. Group 3 **(bottom)**: Active iTBS over ECRL + active cTBS over FCR.

Peripheral stimulation intensity was individualized based on the peripheral motor threshold (PMT). For each participant, the coil was placed over the target muscle (FCR or ECRL) and the intensity was gradually increased from 20% of maximum stimulator output (MSO). The PMT was defined as the lowest intensity that consistently evoked a visible and palpable muscle twitch without causing pain or discomfort.

The final stimulation intensity was set at 110%−120% of the individual's PMT, corresponding to an average of 38.4% ± 9.2% MSO across all participants (range: 25%−52% MSO). This approach of titrating intensity relative to PMT is a established methodology in the field (11). The selected intensity range was designed to ensure adequate afferent input by consistently eliciting a robust M-wave, a key indicator of effective peripheral activation used in previous studies (19).

To ensure stimulation consistency across sessions, the evoked M-wave amplitude was recorded at the beginning and end of each treatment session using surface EMG (1,000 Hz sampling, 50–500 Hz bandpass filter). The target M-wave amplitude for effective stimulation was set between 5 and 10 mV, a range that indicates strong, suprathreshold activation of the peripheral nerve-muscle circuit, which is considered necessary for inducing plasticity. If the amplitude deviated by >20% from the baseline value, the stimulation intensity was recalibrated to maintain consistent peripheral activation. The overall safety of applying pTBS within these parameters in stroke survivors has been supported by systematic appraisal of the literature (20).

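### The PMT-variability rule infers a need for closed-loop titration from poor responders with high CV alone, with no low-CV comparison, and is mislabelled as adaptive

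*Protocol article*

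**What the plan says.** The Discussion reports, from an unpublished pilot, a phenotype "characterized by PMT variability (CV > 15%) in 23% of participants". It continues: "Rather than treating this as statistical noise, we will use it as a predictive feature", and then gives the inference to be drawn: "poor responders with high CV will signal the need for EMG-closed-loop titration in future protocols". On the status of this rule it says "This is an adaptive design element nested within the trial logic, not a" and ends the sentence by denying that the rule is post hoc.

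Three other places bear on the point.

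- **Statistical analysis.** The one association analysis described is a Spearman correlation between change in MEP amplitude (or cortical silent period) and change in FMA-UE. CV does not appear.
- **Theta burst stimulation protocol (text after Figure 3).** PMT is found by raising the intensity over each target muscle. At every session the M-wave is recorded, and "If the amplitude deviated by >20% from the baseline value, the stimulation intensity was recalibrated to maintain consistent peripheral activation".
- **Outcome measures.** A sustained MAS decrease of at least 1 point is called clinically meaningful, and a range for the FMA-UE is cited. The article does not say which measure, or what change, makes someone a poor responder.

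**The concern.** To call CV predictive is to say that response differs between participants with high and low CV. The stated rule looks only at participants who have both high CV and a poor response. How many there are depends on how common high CV is and how common poor response is, and such participants will occur even if the two are unrelated. The rule gives no comparator and no count that would trigger the signal.

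What is at stake is the advice carried forward. A later protocol could adopt a different titration technique on evidence that would look much the same whether or not threshold variability matters. Calling the rule adaptive and not post hoc adds to this, because it presents the inference as a prespecified part of the design.

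**Working it through.** **Inputs from the article.** The high-CV share is 23% (Discussion). The sample is 54, since "we will recruit 18 participants per group, for a total sample size of 54", with at least 45 expected to complete (Sample size estimation).

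**Assumptions, not in the article.** The poor-response rate q is varied from 10% to 70%. Two triggers are tried, at least one and at least three such participants.

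**Step 1: why one cell is not enough.** Take 54 participants, 12 with high CV (0.23 × 54 = 12.4) and 42 with low CV. Suppose 4 of the 12 respond poorly, which is 33%.

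- If 14 of the 42 low-CV participants respond poorly (33%), CV is unrelated to response.
- If 28 of the 42 do (67%), high-CV participants do better.

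The cell named by the rule holds 4 people in both cases.

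**Step 2: what chance alone produces.** With no association, each participant falls in the cell with probability p = 0.23 × q. The expected count is N × p, and P(at least one) = 1 − (1 − p)^N. For q = 30%, p = 0.069:

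- N = 45: expected 45 × 0.069 = 3.1; P = 1 − 0.931^45 = 96%.
- N = 54: expected 54 × 0.069 = 3.7; P = 1 − 0.931^54 = 98%.

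| q (assumed) | Expected, N = 45 / 54 | P(at least 1), N = 45 / 54 | P(at least 3), N = 45 / 54 |
|---|---|---|---|
| 10% | 1.0 / 1.2 | 65% / 72% | 8% / 13% |
| 20% | 2.1 / 2.5 | 88% / 92% | 34% / 46% |
| 30% | 3.1 / 3.7 | 96% / 98% | 61% / 73% |
| 50% | 5.2 / 6.2 | 99.6% / 99.9% | 90% / 96% |
| 70% | 7.2 / 8.7 | >99.9% / >99.9% | 98% / 99.5% |

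**Step 3: what a comparison would do.** As a simplified check, compare the proportion of poor responders in high- and low-CV participants with a two-sided Fisher exact test at 5%, ignoring arm. The groups are 10 vs 35 (N = 45) or 12 vs 42 (N = 54). With no association, and a common poor-response rate of 30% or 50%, the test rejects in about 3.0% to 3.4% of trials. Its power, for assumed poor-response rates in low- vs high-CV participants, is:

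| Low CV vs high CV | N = 45 | N = 54 |
|---|---|---|
| 30% vs 50% | 18% | 20% |
| 30% vs 60% | 34% | 41% |
| 30% vs 70% | 56% | 66% |
| 30% vs 80% | 78% | 87% |

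The comparison controls the false signal but is imprecise unless the difference is very large.

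**Step 4: the adaptive label.** Set side by side, the passages show that the rule applies to later protocols, while the one described adjustment of intensity within this trial is triggered by M-wave amplitude. No described allocation, treatment or analysis step uses CV.

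**The case against.** The best defence is that this is a remark in a Discussion, not a formal decision rule. The same sentence speaks of a predictive feature, and testing prediction ordinarily means relating CV to response in everyone. Such a test may sit in an analysis plan that is not shown, so the absence of CV from the Statistical analysis section is not itself a fault. This much stands, and it is why the point is minor. But the article does state the inference it will draw, and presents it as built into the trial. As stated, that inference has no comparator.

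The defence is also right that the probabilities depend on assumptions. No passage says that one participant is enough, and none gives a poor-response rate. If three were needed and 10% responded poorly, the chance figure would be only 8% to 13%.

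Three stronger readings are tempting, and the documents do not support them.

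- *No repeated PMT is planned, so the CV cannot be computed.* The article is silent on repeat PMT; it does not rule it out. Absence from the assessment schedule (Table 1) proves little, since that table also omits the M-wave recordings made at every session. What can be said is that the article does not identify the readings behind the CV. A recalibrated intensity is not a PMT and arises only when triggered.
- *The 23% is an error.* A reader might tie it to the Discussion's other statement, "approach emerged from pilot data (*n* = 12) where cTBS alone reduced MAS scores without improving ARAT". No count out of 12 gives 23% (2/12 = 16.7%, 3/12 = 25.0%). But the article does not say that the two pilots are the same, and 3/13 = 23.1% would fit.
- *The CV is a post-randomisation variable.* That would hold if it were taken across treatment sessions, which the article does not say.

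**Conclusion.** The point holds in a limited form. The stated inference conditions on one cell of the CV-by-response table, so followed as written it cannot tell a predictive feature from coincidence. With no association, about 3 to 4 poor responders with high CV would be expected at an assumed poor-response rate of 30%, and about 1 at 10%. It would go too far to say that the rule is bound to fire: that depends on a trigger and a response rate that the article does not give.

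The adaptive label is wrong on the article's own description.

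Severity is minor. Nothing here alters allocation, treatment or the comparison between arms; it affects an exploratory conclusion meant for future protocols.

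**What to change.** - Compare change in MAS and in FMA-UE between high- and low-CV participants, adjusted for arm, and report the difference with a confidence interval. Label the analysis exploratory.
- Say that closed-loop titration will be suggested for study only if the high-CV group responds worse. No arm uses that technique, so even a clear difference would be a reason to test it, not proof of need. If the term poor responder is kept, define it.
- State which PMT readings the CV is computed from. If CV is to serve as a baseline predictor, use readings taken before treatment. Readings repeated within one visit may not capture variation between sessions, so the choice should match the phenotype meant.
- Delete the adaptive label.
- For clarity, give the numerator and denominator of the 23%.

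The cost is mainly wording and one exploratory analysis, plus a few minutes of threshold-finding at baseline if repeat readings are not already taken. The downside is a weaker claim: with about 10 to 12 high-CV participants, or 3 to 4 per arm, the interval will be wide.
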